### Data collection and management

After registration, participants will be assigned randomly generated identification codes. They will be asked to keep and use the code to avoid inserting sensitive personal data during their participation. Correspondence between the code and participant’s personal information (e.g. name; contact information; clinical identification in IPOP) is stored in a metadata file that is encrypted with a password and accessible only through the IPOP’s computer, which is protected by institutional security measures.

Data on sociodemographic and health self-report, screening, and primary and secondary outcome measures will be stored in the online survey service used here, LimeSurvey, which adheres to user privacy policies. Data will be periodically copied to an IPOP computer, where they are processed and inserted into excel files. These files will only be accessible to members of the IPOP research team via passwords or physical keys to open specific doors in the case of paper-based documentation, which will be kept in cabinets and locked.

Biological marker data will be obtained from blood samples collected from participants using a 21- to 23-gauge needle into 3 EDTA tubes (≤ 12 mL) and 1 nonadditive tube (4 mL). The standard tubes are stored at 4 °C for a maximum of 180 min. Tubes will be centrifuged at 2500*g* for 30 min at 4 °C. The upper third of plasma will be transferred to sterilized 2 mL tubes, and the plasma samples will be aliquoted and stored at − 80 °C in the hospital biobank until further use. The tubes will be labelled with a reference to the MindGAP project and a participant identification code to ensure anonymization during the blood collection and processing. Prior to EV isolation, a centrifugation step at 5000*g* for 15 min is performed in thawed plasma samples, to remove most of the remaining platelets.

For both self-reported and biological data, a privacy impact assessment has already been submitted, analysed, and approved by the IPOP’s Data Protection Officer.

### Statistical methods

Screening data for errors and missing values is the first step in the data analysis plan. Missing data will be managed and avoided during the data collection by using mandatory fields in the online surveys and retrieving the data from participants when possible. Data from participants who completed fewer than 4-weekly online MBCT sessions will not be considered further, as four sessions were set as the minimum number required for participation [14].

For each group (MBCT and TAU), a summary of baseline sociodemographic and health data will be provided, including number and percentages, mean, standard deviation, median, first and third quartiles, minimum and maximum. Using the sociodemographic and health data, as well as the primary and secondary measures, comparisons will be made between groups to examine whether there are differences between groups at baseline. Similarly, differences at baseline between participants who will complete the study and those who will drop out will be examined. The presence of differences in variables may warrant the need to examine and/or adjust for their influence on outcome changes in the primary analyses. This summary also presents the within-group effect sizes (Cohen’s *d*—equation 11.10, from [135]) for each outcome across time (i.e. T1 to T2; T1 to T3; T1 to T4; T1 to T5).

The total scores of each primary and secondary measure will be used as outcomes in multiple linear mixed models (LMMs). Each model will include the interaction between group and time, while participants will be treated as a random effect. The visual inspection of Q-Q plots will be conducted to check the normal distribution of residuals. Examination of factors such as sex, type of cancer, and cancer stage will be approached by running separate models for each factor. LMM analyses can be employed using, for instance, lmer4 [136] and lmerTest [137] in R software [138].

Descriptive statistics for feasibility indicators (see “Adherence and feasibility” section) will be documented. In the case of programme satisfaction, a qualitative analysis of the information collected in the semi-structured interview, focus groups, and CCI will be conducted [98]. For this purpose, a computer-assisted thematic analysis will be used, following Braun and Clarke’s 6-step approach [139] (see also [140, 141]): (i) familiarization with the data (transcribing the non-written data to a written format and carefully reading all the material several times to become familiar with it); (ii) initiation of the coding process (identifying emergent units of meaning—codes—that are relevant to the research and can be used to tag similar data); (iii) generation of potential and broader themes (codes can be categorized according to the themes and a thematic map that contains associations between themes, including major and sub-themes, and between codes); (iv) review the themes (themes are reviewed to verify if they fit the coded data so that they can be deleted, modified, merged and/or separated; also, the accuracy of the thematic map is reviewed); (v) description of themes (provide a name, characterization, and a scope, and refine the themes step by step); (vi) report of analysis (write and describe in detail the process of analysis using data supporting the themes and discuss the results in light of the literature and research goals). As recommended, steps 1–3 will be conducted by at least two independent researchers and later brought into the group discussion to promote thematic and code reliability [142].

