A secondary objective is to monitor the direct impact of online MBCT on the overall immunological response (objective measure). For this purpose, several biochemical markers in the blood will be evaluated, including the inflammatory response of interleukins IL-1, IL-6, IL-8, IL-10, IFN-γ, and TNF, and C-reactive protein. Other biomarkers that are related to cancer recovery after disease termination are also evaluated, including telomerase activity, antigens related to cancer (cancer antigen—CA 15-3; prostate-specific antigen—PSA; carcinoembryonic antigen—CEA), and other health-related markers (adrenocorticotropic hormone; erythrocytes; glycosylated haemoglobin). While biomarkers of cancer recovery are routinely monitored in recovered patients, biomarkers of immunological response are intended to provide a more general picture of the impact of MBCT upon the overall immunological response. This is important to generate relevant data to support any scientific conclusion about the mind-body interaction.

Similarly, secondary subjective psychosocial parameters are also considered, namely quality of life, fear of cancer recurrence, emotion suppression, mindfulness abilities, sleep quality, posttraumatic growth, health-related behaviours (physical activity; nicotine dependence), and perceived social support. Care was taken to select brief measures, to minimize participant burden.

To evaluate these global objectives, a one-site two-arm parallel randomized controlled superiority study with a 1:1 allocation ratio to internet-supported MBCR vs. TAU will be conducted, with outcomes measured at five distinct time points: (1) baseline; (2) 4 weeks after baseline (mid-point of the intervention, some self-report measures only); (3) 8 weeks after baseline (post-intervention); (4) 24 weeks after baseline; and (5) 52 weeks after baseline. The last two time points will provide evidence for evaluating the long-term effects of online MBCT.

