### Intervention procedures

A schematic representation of the study design from recruitment to the final follow-up time point is provided in Fig. 1. Briefly, after enrolling in the study, participants must complete the baseline survey, which consists of both biological and self-assessments. It is worthy to note that the self-reported measures are being completed via online surveys, while the biomarkers require the participants to visit the hospital for a blood sample collection. The blood samples will be preferably collected during routine clinic visits that occur in all recovered patients. After completing the baseline, participants will be randomized to one of the study conditions, internet-based MBCT or TAU. Subsequent study time points are at 4, 8, 24, and 52 weeks after baseline.

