#### Treatment as usual (TAU)

Participants in TAU group will follow the routine intervention protocol established by the hospital for needs assessment, referral, follow-up, and management of individuals with significant distress difficulties. Participants will be monitored for recurrence of cancer or other health problems, changes related with pharmacological and non-pharmacological interventions, and the occurrence of other major life events.

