#### Criteria for discontinuing intervention

In the group receiving MBCT, along with the weekly daily practice survey, participants will be asked to rate their participation in the programme, from harmful to helpful. This will allow monitoring, identifying, and preventing unwanted effects associated to the intervention. If a negative effect is identified, the difficulties will be explored and could result in the intervention being discontinued for those participants. In addition, all participants have the right to terminate their participation at any time. Whenever possible, information about the main reason(s) for dropping out will be requested and recorded.

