#### Adherence and feasibility

Implementing strategies to promote adherence and prevent dropout is of paramount importance, especially considering dropout rates ranging from 12.1 to 32% in intervention groups [23, 32, 40, 47, 49, 52, 84] and variability in adherence in online programmes ranging from 52 to 83% [14]. Such strategies are also relevant when considering adherence in daily practice. Although current data are heterogeneous regarding the frequency and timing of home practice in online MBIs [14], MBIs are estimated to have an adherence rate of approximately 60% [92, 93]. In addition, studies reported that participants completed between 2 to 4 home exercises per week for online MBIs [46, 94]. Other studies documented reasons underlying for dropping out of online MBIs [21, 40, 52], including technical problems, insufficient technology-related skills, perceived high intensity of the programme, time commitment, lack of motivation, and cancer recurrence or other physical problems.

To avoid technological issues, efforts will be made to provide participants with information on how to complete the online surveys; what is required and how to participate in the videoconference sessions; steps to request specific assistance; in addition to answers to other questions that arise during the study that will be compiled and delivered to participants. Written instructions with step-by-step help information and links to online tutorials will be provided. In addition, interested participants may test the videoconference programme, equipment, and internet in a short session prior to the start of the intervention programme.

Issues such as the intensity and time commitment required by the programme and the compatibility of the programme with daily activities have been identified in the literature as significant barriers to participation [24, 34]. Therefore, flexibility in daily practice is expected. Previous findings suggested that participants prefer short, 10-min mindfulness meditations and more frequently employ body scan exercises, followed by formal sitting meditations, loving-kindness meditations, mindful yoga, and silent meditations [47]. This highlights the need to adapt home practice to a daily routine and offer different exercises with varying lengths to easily accommodate individual preferences [44, 47, 51].

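### Excluding MBCT participants with fewer than four sessions is a one-arm, post-randomisation exclusion, and no analysis of everyone randomised is stated

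*Protocol article*

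**What the plan says.** The Introduction describes "a one-site two-arm parallel randomized controlled superiority study with a 1:1 allocation ratio". Under Intervention procedures the order is baseline first, then allocation: "After completing the baseline, participants will be randomized to one of the study conditions, internet-based MBCT or TAU".

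Statistical methods then sets the analysis population in one sentence: "Data from participants who completed fewer than 4-weekly online MBCT sessions will not be considered further". The reason given is a minimum dose: "as four sessions were set as the minimum number required for participation". The sentence carries no qualification and comes before the baseline summaries and the mixed models, so it governs the primary analyses.

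The control arm has no sessions to attend: "Participants in TAU group will follow the routine intervention protocol established by the hospital". No attendance or equivalent rule is set for it.

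For the MBCT arm, Criteria for discontinuing intervention adds: "If a negative effect is identified, the difficulties will be explored and could result in the intervention being discontinued for those participants".

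The article mentions neither an analysis of all randomised participants nor a sensitivity analysis that keeps the low attenders.

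**The concern.** Randomisation protects a comparison only while people are analysed in the arms to which they were allocated. Here MBCT participants are selected on something they do after allocation, and TAU participants are not. The MBCT people who stay in have shown that they were willing and able to keep attending. Their counterparts in TAU, who would have stopped early if offered MBCT, cannot be identified and remain in the comparison.

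Adherence and feasibility lists reasons for leaving online programmes that include low motivation, cancer recurrence and other physical problems. These could plausibly bear on distress or on blood markers. Someone whose programme is stopped for a negative effect before the fourth session has at most three sessions, and so also leaves the effect estimate.

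The rule applies to both primary outcomes (DASS-21 distress and CNS-EV cargo) and to every secondary outcome modelled the same way. At stake is whether the result can be read as the effect of being offered MBCT.

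**Working it through.** **1. Who can be excluded.** Read literally, the rule would also delete every TAU participant, since all of them complete zero MBCT sessions. The only workable reading is MBCT alone. Attendance starts after allocation, so the criterion is post-randomisation and confined to one arm. This step needs no arithmetic, and the finding rests on it.

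**2. The plan's own numbers.** Sample size estimation gives 84 participants before dropout and adds 27 for 32% dropout: 84 × 1.32 = 110.88, rounded to 111. This reproduces the stated figure. At 1:1 allocation that is 111 / 2 = 55.5 per arm.

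**3. Number excluded (assumption).** The article does not give the share expected to fall below four sessions. The closest proxy is the cited intervention-arm dropout of 12.1–32%. On that basis 55.5 × 0.121 = 6.7 to 55.5 × 0.32 = 17.8 MBCT participants are excluded, about 7 to 18, and none from TAU by rule.

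**4. What can be biased.** The planned model contains a group × time interaction and a random participant effect, with baseline among the time points. A stable difference in level between attenders and non-attenders goes into the group main effect. The interaction is biased only if attendance is related to *change* in outcome. So let r be the correlation between attendance and favourable change. The article gives no value; 0, 0.2 and 0.3 are assumed.

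**5. Formula.** Assume no true effect and normality. If the lowest fraction q on attendance is removed from MBCT, the mean change of those kept shifts by

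bias = r × φ(z_q) / (1 − q),

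in SDs of change, where z_q is the q-quantile of the standard normal.

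- q = 0.121: z = −1.170, φ = 0.2012, ratio 0.2012 / 0.879 = 0.229.
- q = 0.32: z = −0.468, φ = 0.3576, ratio 0.3576 / 0.68 = 0.526.

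The standard error is √(1/[55.5(1 − q)] + 1/55.5), which is 0.196 at q = 0.121 and 0.211 at q = 0.32. Two-sided type I error is Φ(−1.96 + bias/SE) + Φ(−1.96 − bias/SE).

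| Assumed r | Bias, q = 12.1% | Type I error | Bias, q = 32% | Type I error |
|---|---|---|---|---|
| 0 | 0 | 5.0% | 0 | 5.0% |
| 0.2 | 0.046 SD | 5.6% | 0.105 SD | 7.9% |
| 0.3 | 0.069 SD | 6.4% | 0.158 SD | 11.6% |

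A negative r would reverse the sign of the bias.

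**6. Cross-check.** Bias also equals q × g, where g is the gap in mean change between those kept and those excluded. With g = 0.5 SD this gives 0.121 × 0.5 = 0.06 and 0.32 × 0.5 = 0.16 SD, close to the r = 0.3 row.

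**7. Limits.** This is a two-group comparison of change, not the full mixed model. It counts every excluded person as someone who would have supplied follow-up data. Those who leave altogether would be missing with or without the rule, so the rule's own contribution is smaller to the extent that the two groups overlap.

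**The case against.** **A separate analysis plan might define the population properly.** It might exist, but the article does not leave the matter open. It states the exclusion, so a plan that kept everyone would contradict it and one of the two would still need correcting.

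**Four sessions is a reasoned minimum dose.** That supports a secondary analysis of people who received the dose. It does not support making a one-arm exclusion the only stated analysis.

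**The plan compares completers with dropouts at baseline and may adjust.** This is a partial safeguard. It does not bring the excluded people back, and it cannot adjust for unmeasured motivation or for events after baseline.

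The other side is right about several stronger readings that a reader might infer:

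- *That the bias certainly favours MBCT.* The article does not fix the sign. Its reasons for leaving also include technical problems, limited technology skills and time commitment, which need not be prognostic.
- *That TAU keeps everyone.* It does not. Sample size estimation cites control dropout of 6–17.4%, and 19.6% at follow-up. TAU is spared only removal by rule.
- *That 17–48% of MBCT would be excluded.* Adherence and feasibility reports "variability in adherence in online programmes ranging from 52 to 83"%, but does not define adherence as attending four sessions. The complement is therefore not the share below the threshold.
- *That early harms vanish from the report.* Oversight and monitoring says incidents are documented in the participant flow diagram, and reasons for dropping out are recorded where possible. Such people leave the effect estimate, not the trial record.

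**Conclusion.** The point stands and should be corrected before analysis. The stated rule conditions one arm on post-randomisation behaviour, and nothing in the article restores the randomised comparison for either primary outcome. That conclusion does not depend on any assumed number.

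A tilt towards MBCT is the likely direction, not an established one. The illustrated size, about 0.07–0.16 SD with a type I error of about 6–12%, rests on three assumptions: the share below four sessions equals the cited 12.1–32% dropout, attendance correlates 0.3 with change in outcome, and the excluded people would otherwise have supplied follow-up data. None of these is in the article. The bias is zero if attendance is unrelated to change.

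**What to change.** Replace the exclusion sentence with wording such as: *All randomised participants are analysed in their allocated arm using all available data, whatever number of sessions they attended; surveys and blood collection continue after sessions stop.* The planned mixed models can already use partial follow-up.

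Keep the four-session threshold only for a secondary analysis labelled as such. A complier-average estimate is one option.

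Oversight and monitoring already gives the route for the change: ethics committee first, then the registry. It is best made before anyone analyses the data, since the Blinding section says the data analysts will not be blinded.

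The cost is a paragraph of wording, continued survey invitations to people who stop attending, some further blood-collection visits with travel reimbursed, and possibly a smaller estimate. The change does not solve missing data from people who leave the study altogether.

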#### Sample size estimation

Because no previous study has examined circulating EVs in relation to MBIs and cancer, we could not use a specific effect size in estimating the sample size. Nonetheless, a recent systematic review examining the effects of Internet-based MBIs on psychological distress (anxiety and depression) found a median Cohen’s *d* value between 0.38 and 0.42 for the other primary outcome, psychological distress [14]. By using G*Power-3.1 statistical software [82] and considering repeated-measures ANOVA related to within-between interaction (group × time interaction), with an alpha significance level of 0.05 and an effect size of 0.38 (as calculated in [83]), a sample of 84 participants would allow for a power of 0.80. Additionally, previous studies showed dropout rates ranging from 12.1 to 32% for the intervention group and from 6 and 17.4% for the control group, when considering the period immediately following the intervention [23, 32, 40, 47, 49, 52, 84]. At follow-up, dropout rates were about 30.8% in the intervention group and 19.6% in the control group [52]. Considering the highest dropout rate (32%), 27 participants should be added to the estimated sample, resulting in a minimum of 111 participants to be included in the study.

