#### Blinding

Prior to randomization, individuals involved in the study (participants, study coordinators, mindfulness instructor(s), research assistants, statistician) will be blinded to the study conditions. After randomization, the research team will inform participants about group membership. Similar to previous studies in the field [14], and given the specificities and resources available in the current study, it is impossible to guarantee further blinding of participants and staff irrespective of their role. This unblinding also applies to the data analysts as most of the team members involved in the data collection will participate in the data management and analysis. Even so, the team members not collaborating directly in the data collection, such as the team dedicated to the characterization of the CNS-derived EVs, will be blinded to the study conditions where possible.

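### Observed baseline and dropout differences may decide how the primary models are adjusted, with no stated criterion and with analysts who know allocation

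*Protocol article*

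**What the plan says.** The Statistical methods section of the protocol article starts from the sociodemographic and health data and the primary and secondary measures. On these, "comparisons will be made between groups to examine whether there are differences between groups at baseline". It then plans a baseline comparison of participants who complete with those who drop out. The consequence drawn from both is: "The presence of differences in variables may warrant the need to examine and/or adjust for their influence on outcome changes in the primary analyses".

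The section names no test, no threshold, no list of candidate covariates and no form of adjustment. The model it does describe is a linear mixed model with a group-by-time interaction and a random participant effect. Sex, cancer type and stage are to be looked at in separate models.

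The Allocation section mentions randomisation blocks but no stratification factor that would define a covariate in advance. On who makes the choice, the Blinding section says: "This unblinding also applies to the data analysts".

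**The concern.** This is a rule written into the plan, not a detail left to a later document. It has three weaknesses.

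- **The between-arm trigger uses the wrong criterion.** With proper randomisation, any baseline difference between arms is chance. Its size says nothing about whether the variable predicts the outcome. A strongly prognostic variable that happens to be balanced stays out, and an irrelevant one that happens to be unbalanced may come in.
- **The dropout trigger comes late.** Who drops out is known only during follow-up, so the primary models cannot be final until outcome data exist.
- **The decision is discretionary and unblinded.** The wording permits adjustment without requiring it, and the people deciding know the allocation.

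At stake are the credibility of the primary result, because more than one primary model is defensible under the text, and precision that adjustment for the T1 value could provide without further data.

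**Working it through.** **1. The plan's own figure.** The Sample size estimation section states "a sample of 84 participants would allow for a power of 0.80", with alpha 0.05 and 0.38 as the effect size. The allocation is 1:1 and there are five time points (Introduction).

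- Taking the noncentral F for the within-between interaction with f = 0.38 and noncentrality f² × N: 0.1444 × 84 = 12.13, with 4 and (84 − 2) × 4 = 328 degrees of freedom. Power is 0.801, against 0.790 at N = 82. So 84 reproduces.
- 84 × 1.32 = 110.9, hence 111.

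Neither figure depends on covariate adjustment, so the sample size calculation does not settle the model. (The match needs 0.38 to be read as Cohen's f; that is a separate matter.)

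**2. How easily chance would trip the rule.** Assume k independent comparisons, each flagged at 5%. The protocol states neither. P(at least one flag) = 1 − 0.95^k.

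| k | P(at least one) | expected flags (0.05 × k) |
|---|---|---|
| 20 | 1 − 0.95^20 = 0.64 | 1.0 |
| 50 | 1 − 0.95^50 = 0.92 | 2.5 |

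The sociodemographic and health items in Table 3, the questionnaire scores and about 15 biomarkers come to more than 50 variables. Many are probably correlated, so 20 is the more cautious illustration.

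**3. What the rule does to the test.** Simulation with 42 per arm and one follow-up contrast analysed as change from baseline. There were 20 independent baseline covariates, five of them prognostic (together 10% of residual variance), plus the baseline score. Flags were set at p < 0.05 and 25% of participants were labelled dropouts at random. There were 10,000 null runs, and 4,000 runs with a standardised difference of 0.38, for each baseline-to-follow-up correlation rho.

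| | rho 0.3 | rho 0.5 | rho 0.7 |
|---|---|---|---|
| Type I, unadjusted change | 0.050 | 0.047 | 0.057 |
| Type I, prespecified baseline adjustment | 0.053 | 0.048 | 0.049 |
| Type I, automatic adjustment for arm-flagged variables | 0.042 | 0.038 | 0.046 |
| Type I, best of unadjusted and flag-adjusted models | 0.068 | 0.066 | 0.074 |
| Power, prespecified baseline adjustment | 0.43 | 0.51 | 0.68 |
| Power, automatic adjustment for arm-flagged variables | 0.29 | 0.40 | 0.60 |

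The automatic rule used between-arm flags only. The free choice used flags from either comparison. Free choice adds 0.017 to 0.019 to the error of the unadjusted contrast.

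**4. Precision, if T1 is a response with free arm means.** The effect is then a difference in change. With unit variance at each visit, its variance is proportional to 2(1 − rho). With baseline adjustment it is proportional to 1 − rho². The ratio is (1 − rho²) / (2(1 − rho)) = (1 + rho)/2. Power is by noncentral t, 42 per arm, difference 0.38, two-sided 5%, one follow-up visit.

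| rho (assumed) | variance ratio | power, change | power, adjusted |
|---|---|---|---|
| 0.3 | 0.65 | 0.307 | 0.438 |
| 0.5 | 0.75 | 0.406 | 0.511 |
| 0.7 | 0.85 | 0.603 | 0.673 |

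The ratio is below 1 for every rho below 1, so the direction does not depend on the assumed value.

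**The case against.** Several stronger readings are tempting, and the document does not carry them.

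- **That data-driven adjustment will happen.** The text says differences may warrant examining or adjusting. It is an option, and examining could mean a secondary look. This stands. The defect is the open option, not a certain outcome.
- **That the rule necessarily inflates type I error.** It does not. Applied mechanically it was slightly conservative in the simulation. Inflation needs an analyst who picks among models, which the wording permits but does not predict.
- **That the model wastes the baseline.** The plan never says whether T1 is a response or a covariate, or whether the arms may differ at T1. A model with a common T1 mean also contains a group-by-time interaction. Even with free T1 means, the mixed model is valid under randomisation. The precision argument is therefore conditional and concerns efficiency, not bias.
- **That the dropout comparison adjusts for post-randomisation variables.** The variables compared are baseline variables; only their selection uses dropout status. Including baseline predictors of dropout is a recognised way to make a missing-at-random assumption more plausible. That purpose is legitimate, but a labelled sensitivity analysis serves it without leaving the primary model open.
- **That the power figures describe the planned test.** They are for one follow-up contrast, whereas the plan powers an interaction over repeated measurements. They illustrate the direction and rough size of the gain only.

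A statistical analysis plan may exist and may override the rule. The published text nevertheless states the rule, and nothing else in the article limits it.

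**Conclusion.** The point holds in a limited form. The plan allows observed differences between arms, and between completers and dropouts, to decide whether and for what the primary models are adjusted. There is no criterion, and the analysts know allocation. The between-arm part selects covariates on a basis unrelated to prognosis.

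The sizes are conditional. A false flag is likely (64% for 20 variables, 92% for 50) only if the comparisons are independent 5% tests. Used automatically, the rule costs power against prespecified baseline adjustment (0.40 against 0.51 at rho 0.5 in the simulation). Used freely, it puts type I error at about 0.07 instead of 0.05. The 25% variance reduction at rho 0.5 (35% at 0.3, 15% at 0.7) applies to a single-visit contrast, and only if T1 is modelled as a response with free arm means. That is the natural reading of the model, but it is not stated.

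A reader might also infer that the primary model must include cancer type. The documents give no basis for that: no stratification factor is named and no prognostic evidence is cited.

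This does not invalidate the trial. It should be corrected before analysis because the better rule is available at almost no cost.

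**What to change.** In Statistical methods:

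1. Delete the sentence that lets observed differences trigger adjustment in the primary analyses. Keep the baseline table as a description of the arms, without tests.
2. State in advance that every model adjusts for the outcome's own T1 value, whatever balance is observed. Either enter T1 as a covariate for the later visits, or keep T1 as a response and constrain the arms to a common T1 mean. Say which.
3. Make any other adjustment a labelled sensitivity analysis. This includes baseline predictors of dropout used to support a missing-at-random assumption. Adding cancer type to the primary model is optional; if it is wanted, name it now.

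The cost is wording in the protocol and any analysis plan, through the amendment route described under Oversight and monitoring. The T1 values are already scheduled, so no participants, visits or measurements are added.
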